## Methods/design

This is a single-centre, phase II clinical trial in patients undergoing major abdominal surgery (Fig. 1). The study follows a prospective, controlled and open design. Initially, the study will begin with a pilot phase of six patients followed by a randomization phase. An overview of the patients’ schedule of activities according to the Standard Protocol Items: Recommendations for Interventional Trials (SPIRIT) figure is provided in Fig. 2.

**Fig. 1 Fig1:**
[figure not shown]
Participant flow diagram showing the organizational structure and different study groups of PALANCE

**Fig. 2 Fig2:**
[figure not shown]
Patient schedule of activities according to the Standard Protocol Items: Recommendations for Interventional Trials (SPIRIT) figure. *SID* Strong Ion Difference, *SUEs* serious unexpected events, *SUSARS* severe unexpected serious adverse event, *UE* unexpected events, *UO* urinary output

### Pilot phase

The first six patients will receive Jonosteril® together with sodium glycerophosphate (IMP1/IMP2 protocol) in concentrations ranging from 1 to 6 mmol/l (Na^+^: 139–149 mmol/l) to evaluate the most suitable concentration for the following randomization phase. We will test a concentration of 4 mmol/l phosphate (= 2 ml sodium glycerophosphate per 500 ml Jonosteril®) initially. This solution will contain 145 mmol/l sodium. Repeated measurements of serum phosphate levels will shed light on the efficacy of the measure. In the case that serum phosphate levels do not remain stable within the normal range, we will gradually adapt the dose until stable levels are achieved. Patients will not receive a concentration higher than 6 mmol/l since then the sodium levels would surpass the maximum threshold value.

### Randomization phase

After the pilot phase, in which the most suitable phosphate concentration is determined, a total of 42 patients, 21 per group, will be allocated to one of the two study arms by randomization:Jonosteril® and sodium glycerophosphate (IMP1/IMP2) (treatment group)Jonosteril® (IMP1) (control group)

All patients will receive the study medication according to their allocation over 120 min after the initiation of general anaesthesia in a maximum dose of 30 ml per ideal bodyweight (IBW = height (in cm) − 100) per hour for losses due to insensible perspiration, urinary output and extracellular deficits due to the fasting state as well as five times the estimated blood loss [32, 33]. The rationale for the use of the amount of fluids is based on previous studies and the demand-oriented current clinical practice. This is in concordance with previous studies using similar regimes. The recruited patients have a higher fluid demand [32, 33]. Hofmann-Kiefer et al. showed that a maximum of 30 ml/kg/bodyweight was necessary to keep patients hemodynamically stable and distinct acid-base alterations were described. Over the time course of 120 min, the patients likely suffer from a blood loss of 1000 ml or more. According to current clinical practice, a blood loss should be replaced in a ratio of 4–5:1 with crystalloids [33]. Taken together, our approach using 30 ml/kg/ideal bodyweight seems reasonable for this patient cohort. Measurements will take place every 30 min: baseline (T1), 30 min (T2), 60 min (T3), 90 min (T4) and 120 min (T5) and parameters will be documented by the investigators in the Case Report Forms (CRF) of each participant. An overview of the parameters assessed in this study and their respective time points is provided in Table 1.

**Table 1 Tab1:** Parameters measured at the distinct time points

Measurement	Time point
Haemodynamic values	
Norepinephrine dose (mg/h)	T1–T5
Heart rate (min^-1^)	T1–T5
Systolic blood pressure (mmHg)	T1–T5
Diastolic blood pressure (mmHg)	T1–T5
Central venous pressure (mmHg)	T1–T5
Stroke volume variation (%)	T1–T5
Cardiac output (ml/min)	T1–T5
Blood loss (ml)	T1–T5
Haemoglobin (g/dl)	T1–T5
Haematocrit (%)	T1–T5
Urine volume (ml)	T1–T5
Crystalloid administered (ml)	T1–T5
Serum electrolytes	
[PO_4_ ^3-^] ionized (mmol/l)	T0–T5
[PO_4_ ^3-^] (mg/dl)	T0–T5
[Na^+^] (mmol/l)	T1–T5
[K^+^] (mmol/l)	T1–T5
[Cl^−^] (mmol/l)	T1–T5
[Mg^2+^] (mmol/l)	T1–T5
[Ca^2+^] (mmol/l)	T1–T5
Osmolality (mosmol/l)	T1–T5
Renal function	
Serum creatinine (mg/dl)	T0 and T6
Serum urea nitrogen (mg/dl)	T0 and T6
GFR calculated (ml/min)	T0 and T6
Acid-base values	
Anion gap (mmol/l)	T1–T5
HCO3^-^ (mmol/l)	T1–T5
BE (mmol/l)	T1–T5
pH	T1–T5
PaCO_2_ (mmHg)	T1–T5
Stewart acid-base parameters	
[A^-^] (mmol/l)	T1–T5
Strong Ion Difference (mmol/l)	T1–T5
Effective Strong Ion Difference	T1–T5
Strong Ion Gap (mmol/l)	T1–T5
Albumin (mg/dl)	T1–T5
Lactate (mmol/l)	T1–T5
Urine	
[Urinary Na^+^] (mmol/l)	T1 and T5
[Urinary K^+^] (mmol/l)	T1 and T5
[Urinary Cl^−^] (mmol/l)	T1 and T5
[Urinary Mg^2+^] (mmol/l)	T1 and T5
[Urinary Ca^2+^] (mmol/l)	T1 and T5
[Urine osmolality] (mosmol/l)	T1 and T5
[Urinary phosphate] (mmol/l)	T1 and T5
Glycocalyx components	
Syndecan-1	T1–T5
Hyaluronic acid	T1–T5

*BE* base excess, *GFR* glomerular filtration rate

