### Sodium glycerophosphate

Sodium glycerophosphate (Fresenius Kabi AG, Bad Homburg, Germany; concentration 1 mmol/ml, ATC-Code: B05XA) is an electrolyte supplement approved and routinely administered for the parenteral treatment of hypophosphatemia especially on intensive care units (ICUs). Phosphate is usually not routinely measured during surgical procedures and is, therefore, not substituted. Accordingly, a hypophosphatemia occurs frequently with an incidence of between 44.8% [23] and 67% [24] and remains undetected, although the unfavourable effects in terms of post-aggression metabolism are well known. The ATP- dependent metabolism strongly relies on phosphate as a substrate, especially during the postoperative phase of major cardiac and abdominal surgery [25, 26]. This leads to a high turnover of phosphate and requires parenteral substitution. Therefore, an intraoperative substitution of phosphate seems reasonable and indicated. It has been shown that an early perioperative substitution of phosphate during liver surgery had a protective effect in terms of cardiorespiratory complication and is, therefore, recommended [27, 28]. Prior to inclusion, all patients will be evaluated regarding contraindications for the use of sodium glycerophosphate (existing chronic kidney disease or renal failure, hyperphosphatemia, hypernatremia or allergic disposition towards sodium glycerophosphate or its components). If none of the above can be detected, the parenteral application of sodium glycerophosphate is uncritical. By contrast to the dosage given on ICUs [29] or according to an estimated basic daily demand of 0.2–0.5 mmol/kg bodyweight (according to the summary of product characteristics) the amount of phosphate given during this trial is low. The maximum infusion rate is 20 mmol phosphate per hour according to the manufacturer and will not be reached. It is expected that during the observation period and due to the substitution, serum phosphate levels will rise around 0.5 mmol/l [22] which will be controlled every 30 min. Since the substituted phosphate gets rapidly metabolized and excess phosphate is excreted in the urine, a severe hyperphosphatemia is not expected [30]. Before initiation of the trial, it was confirmed that Jonosteril® and sodium glycerophosphate are compatible for the intended use. Phosphate will be added to Jonosteril® immediately prior to the application to avoid any potential risk of infection.

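### The infusion maximum is stated in two ways and cannot hold the blood-loss replacement it is worded to cover, so the assurance on the phosphate rate depends on which reading is taken

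*Protocol article*

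**What the plan says.** All places are in the Protocol article.

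- **Randomization phase, operative sentence.** Study medication is given over 120 min "in a maximum dose of 30 ml per ideal bodyweight". After the definition of IBW (height in cm minus 100) the sentence continues "per hour for losses due to insensible perspiration, urinary output", then names fasting deficits, and ends with "as well as five times the estimated blood loss".
- **Randomization phase, rationale.** An earlier study is cited for a maximum of 30 ml/kg, and the paragraph concludes that "our approach using 30 ml/kg/ideal bodyweight seems reasonable". Neither statement has a time unit. The rationale also expects that "the patients likely suffer from a blood loss of 1000 ml or more" within the 120 min, and it gives a crystalloid replacement ratio of 4–5:1.
- **Pilot phase.** Phosphate is added "in concentrations ranging from 1 to 6 mmol/l". The first concentration tested is 4 mmol/l, and 6 mmol/l is the ceiling.
- **Sodium glycerophosphate.** "The maximum infusion rate is 20 mmol phosphate per hour according to the manufacturer and will not be reached". The section also says that "the amount of phosphate given during this trial is low", compared with ICU dosage and with a basic daily demand of 0.2–0.5 mmol/kg.
- **Power considerations.** The planning fall in [A⁻] of 2.67 mmol/l comes from patients who received 4000 ml over 120 min.

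**The concern.** Three things do not fit together. First, the operative sentence has an hourly unit and the rationale does not, which is a factor of two over the 120 min window. Second, blood-loss replacement is listed among the losses that the maximum covers, yet the expected blood loss at that multiple is larger than the maximum for most women. This invites a different reading, in which the replacement comes on top. Third, the statement about the phosphate rate carries no condition, although the rate is volume times concentration and the volume is not settled.

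The rule governs how the intervention is given. The Background and Jonosteril® sections attribute the fall in [A⁻], the primary endpoint, to dilution by infused fluid. A reader of the article cannot tell what volume bounds the exposure, or which volume the phosphate assurance was derived from.

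**Working it through.** **Inputs from the article.** 30 ml per IBW (read as per kg) per hour; 30 ml/kg without a time unit; 120 min; 5 × blood loss; blood loss of at least 1000 ml; 4 and 6 mmol/l phosphate; 20 mmol/h; 0.2–0.5 mmol/kg per day; 4000 ml over 120 min.

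**Assumptions not in the article.** IBW 65 kg (height 165 cm), range 55–80 kg; blood loss exactly 1000 ml unless stated; all blood-loss replacement given as study solution within the window; rate averaged over the two hours.

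**Volumes at 65 kg**

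- A, 30 ml/kg in total: 30 × 65 = 1950 ml.
- B, 30 ml/kg per hour with blood loss inside: 30 × 65 × 2 = 3900 ml.
- C, B plus replacement: 3900 + 5 × 1000 = 8900 ml.

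Ratios: B/A = 2.0 at any body size; C/B = 2.3; C/A = 4.6 (4.1 at 80 kg to 5.0 at 55 kg).

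**Does the replacement fit inside the maximum?** 5 × 1000 = 5000 ml. On B the cap is 60 ml/kg over two hours, so IBW must be at least 5000/60 = 83.3 kg, before any insensible, urinary or fasting loss. At the 4:1 end of the stated ratio it is 4000/60 = 66.7 kg, again with nothing left for the other losses.

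**Phosphate rate = volume (l) × concentration / 2 h**

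| Reading | 4 mmol/l | 6 mmol/l | Range at 6 mmol/l, IBW 55–80 kg |
|---|---|---|---|
| A | 3.9 mmol/h | 5.9 mmol/h | 5.0–7.2 |
| B | 7.8 mmol/h | 11.7 mmol/h | 9.9–14.4 |
| C | 17.8 mmol/h | 26.7 mmol/h | 24.9–29.4 |

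The article's assurance reproduces on A and B. On B at 6 mmol/l, 20 mmol/h would need an IBW of 20/(6 × 0.030) = 111 kg. On C it is reached in either of two ways at 65 kg:

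- with 1000 ml loss, from 20/(8.9/2) = 4.5 mmol/l upwards;
- at 4 mmol/l, from a loss L with (3.9 + 5L) × 4/2 = 20, so L = 1.22 l.

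At 4 mmol/l and exactly 1000 ml, C stays below 20 (16.6–19.6 mmol/h over IBW 55–80 kg).

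**Dose against daily demand.** On B, 0.060 l/kg × 4 = 0.24 and × 6 = 0.36 mmol/kg IBW in two hours. On A the figures are 0.12–0.18. On C at 65 kg they are 35.6/65 = 0.55 and 53.4/65 = 0.82. The comparator is 0.2–0.5 mmol/kg for a whole day. On B its lower end is reached at 0.2/0.060 = 3.3 mmol/l.

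**Planning volume.** 4000 ml over 120 min corresponds to an IBW of 4000/60 = 66.7 kg on B and 4000/30 = 133 kg on A. It therefore fits B and neither A nor C.

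**The case against.** The strongest reply is that the text has one natural reading: an hourly cap with blood loss among the items it covers. The grammar of the operative sentence supports this, and so does the rationale, which discusses blood loss and then returns to the 30 ml/kg figure. The 4000 ml planning volume matches it too. The unit missing from the rationale may be shorthand. On this reading the phosphate rate is 7.8–11.7 mmol/h at 65 kg and the assurance holds comfortably. The figure is also a maximum within demand-led practice, not a target; it is the same in both arms, and infused volume and blood loss are recorded from T1 to T5.

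Much of this stands. It rules out the inference that the 20 mmol/h limit will be exceeded or that the safety argument fails outright. An excess needs the additive reading, and then either a concentration above about 4.5 mmol/l or, at 4 mmol/l, a loss above about 1.2 l.

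A reader might also infer that the trial is underpowered because a lower volume would shrink the effect. The article does not support that. It would require the fall in [A⁻] to scale in proportion to volume, which is nowhere stated, and it would use the total-volume reading that the 4000 ml figure speaks against.

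On the word low, the ICU comparator is not quantified in the article. Demand is stated per kg bodyweight, so a patient heavier than her IBW receives less per kg than computed here. That part is therefore minor.

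What the reply does not remove is the misfit on the natural reading itself: the cap cannot contain five times the expected blood loss for most IBWs. Nor does it help that a journal article condenses the full protocol, because these are conflicts between printed statements, not omissions. Phosphate checks every 30 min are a safeguard, but they do not make an unconditional statement correct.

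**Conclusion.** The point holds as an inconsistency that should be fixed, not as evidence of unsafe exposure or a wrong sample size. The unit conflict is a factor of two at any body size. The blood-loss item alone exceeds the two-hour maximum for any IBW below about 83 kg, given the article's own lower figure for blood loss. At an assumed IBW of 65 kg the readings span 1950, 3900 and 8900 ml. The phosphate assurance is true on the two capped readings and untrue on the additive one at the highest permitted concentration (26.7 mmol/h; 24.9–29.4 over IBW 55–80 kg). The description of the amount as low against daily demand is, at 4–6 mmol/l, borne out only on the 30 ml/kg-in-total reading. These figures rest on the assumed IBW, on replacement being given as study solution, and on averaging over 120 min. No view is taken on which volume, rate or concentration is right.

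**What to change.** Reconcile the Randomization phase, Pilot phase, Sodium glycerophosphate and Power considerations sections into one volume statement. It should say whether the maximum is per hour or in total, and whether blood-loss replacement lies inside or outside it.

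From that statement:

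1. Recompute the maximum phosphate per hour and per kg at the highest permitted concentration, and show the calculation.
2. Correct or qualify the assurance about 20 mmol/h and the word low wherever the recomputed figures do not support them.
3. Confirm that the 4000 ml over 120 min behind the planning assumption is consistent with the reconciled statement.

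The cost is a protocol clarification and a short recalculation. The point itself calls for no change in sample size; the planning assumption would need another look only if step 3 fails.

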### Anaesthesiologic management and postoperative care

All patients will receive anaesthesiologic management according to the institution’s standard. This involves a thoracic epidural anaesthesia in combination with general anaesthesia and the placement of a central venous line and an arterial catheter for haemodynamic monitoring. In case of contraindications to neuroaxial procedures patients will receive general anaesthesia and, postoperatively, patient-controlled analgesia with piritramide. Anaesthesia will be induced with propofol (2 mg/kg), sufentanil (0.4 mg/kg) and rocuronium (0.6 mg/kg) and maintained with propofol and remifentanil or sevoflurane in patients with certain conditions (e.g. cardiopulmonary diseases). The pulmonary ventilation will be standardized in all patients using the volume-controlled mode in order to keep the paCO_2_ at 40 ± 3 mmHg as to have as little influence on acid-base balance as possible (controls are performed using blood gas analysis). The epidural anaesthesia will be continued for at least 3 days and will be combined with nonsteroidal anti-inflammatory drugs. Intraoperative hemodynamic monitoring will be performed using a PulsioFlex monitor with ProAQT® sensor (PULSION Medical Systems SE, Germany). The observation period will be 120 min after initiation of anaesthesia although surgery will take longer in most cases. The administration of the study drug, e.g., sodium glycerophosphate, as well as study-specific blood draws, will take place only during the 120 min of the procedure. Afterwards, the anaesthetist responsible for the patient will continue according to clinical standards. All patients will be transferred from the operating room to the ICU for postoperative surveillance and will be visited by in-hospital postoperative pain management service staff daily.

### Trial population and selection criteria

Patients are identified based on their diagnosis and scheduled surgery at the department of gynaecology. We recruit only female patients who are scheduled for major abdominal surgery, i.e. laparotomy. By routine, these patients will undergo placement of a central venous line and an arterial line. Laparoscopic or transvaginal approaches are not included. We screen eligible patients for study participation according to the predefined inclusion and exclusion criteria and provide information regarding the trial during a pre-operatory orientation interview with one of the investigators of the team. We will obtain informed consents from all participants of the study. In addition to informed consent regarding the participation in the study, the patient will be asked to sign a separate informed consent for the frozen storage and possible use of blood samples for scientific purposes to address comments of reviewers during the publication phase. The latter consent is independent of participation in the study. Patients receive complete information about the trial and enough time to consider participation.

#### Inclusion criteria

Subjects must meet the following inclusion criteria to be eligible for enrolment:Female patients (ASA Classification I–III) who are scheduled for a major abdominal surgical procedure under general anaesthesia with routinely planned placement of a central venous and an arterial catheter and who have given written informed consentAge ≥18 years

#### Exclusion criteria

Subjects showing the following exclusion criteria cannot be included in the trial:Participation in another clinical trialPatients who are not personally able to give their informed consentPatients at a childbearing age without using contraceptivesAcute or chronic renal failure (glomerular filtration rate <60 ml/min)Patients suffering from an acid-base-disturbance (i.e. severe acidosis)Patients suffering from acid-base disturbances caused by SIRS or sepsisPregnancy or lactation period (pregnancy testing will be executed at least 1 day prior to the surgical procedure)Oedema, hypertonic dehydratation, hyperhidratationHyperphosphata emia, hypernatraemia, hypocalcaemia (according to the standard normal laboratory values of the authors’ institution)A known hypersensitivity against the test drugs and/or their componentsA known history or active abuse of alcohol and/or drugs

### Randomization

INPADS GmbH performs the allocation of patients to one of the two study arms using simple, balanced randomization via random numbers. A computer-generated number between 0 and 1 is subsequently analysed as to whether it lies above 0.5 (allocation to IMP1) or below 0.5 (allocation to IMP1 and IMP2 combined). The randomization procedure is executed for all patients after the pilot phase undergo the randomization procedure and a list is generated prior to first patient’s first visit (FPFV).

### Statistical evaluation

#### Power considerations

This study aims to show that [A^−^] can be stabilized by applying IMP1/IMP2 in a combined approach. In a previous investigation of our group, [A^−^] was reduced by 2.67 ± 2.4 mmol/l in patients who had received 4000 ml of Jonosteril® over 120 min [22]. We expect that we can counteract the decrease in [A^−^] up to 60% when using the IMP1/IMP2 protocol. This will presumably result in an average difference in [A^−^] of 1.602 mmol/l in the treatment group. Furthermore, we assume that [A^−^] will be more stable over all time points. As a consequence, the range of [A^−^] will be lower in the treatment compared to the control group. Therefore, we expect that the standard deviation will rather be 1.8 mmol/l than 2.4 mmol/l (estimated reduction of 30%) [22].

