#### Sample size calculation

We calculated the sample size using the statistic software SAS (SAS Institute GmbH, Heidelberg, Germany). This study has an explorative character and is supposed to deliver first-ever data. There is currently no comparative data available for the medication group or time intervals considered. For the control group regimen, there is data available from a previous study [22] for two time points (60 min and 120 min after exposure). Therefore, we considered the deviation of [A^−^] at the time point T5 (120 min) compared to baseline T1 (0 min) applying a *t* test. We expect normally distributed data since the control group data derived from the previous study showed the same characteristics [22]. We set the level of significance to 5% and the power to 80% resulting in 21 patients per group. With the addition of swix patients for the pilot phase, the total number of patients is 48.

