#### Analysis procedure

The primary objective of the study is to show that during the observation period of 120 min the mean values of [A^−^] display a lower deviation in the treatment group when compared to the control. We will evaluate normal distribution using the Kolmogorov-Smirnov test. To test for differences between two study groups with normally distributed data, a two-sample *t* test will be used. In order to evaluate differences of [A^−^] within one study group over time, we will perform a RM-ANOVA with a *t* test for paired samples as post hoc. We will analyse data that does not follow a normal distribution using the Friedman test. Level of significance for all calculations is defined at 5%. We will analyse secondary parameters descriptively and calculate mean, number, minimum, maximum, 1st quartile, 3rd quartile, mean standard error and standard deviation (SD) (method of aggregation: continuous). Further analyses and testing procedures can be defined at a later stage. The primary statistical analysis is based on the “intention-to-treat” principle. Safety data (UE, SUE, SUSARs) will be analysed descriptively in all groups at least every 12 months.

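### With 21 per group, 80% power (two-sided) needs an SD of 1.8 in both arms, but the plan justifies that SD only for the treatment arm; with 2.4 in the control arm, power is about 66%

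*Protocol article*

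**What the plan says.** All the inputs are in the protocol article, under Statistical evaluation.

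- **Earlier data (Power considerations).** In the group's previous study, [A⁻] "was reduced by 2.67 ± 2.4 mmol/l in patients who had received 4000 ml of Jonosteril® over 120 min". The section Sample size calculation treats that study as the source of data for the control regimen.
- **Effect (Power considerations).** The combined regimen is expected to counteract up to 60% of the fall: "This will presumably result in an average difference in [A^−^] of 1.602 mmol/l in the treatment group".
- **Spread (Power considerations).** The authors assume that [A⁻] will be steadier over time under treatment. "As a consequence, the range of [A^−^] will be lower in the treatment compared to the control group". From this they conclude that the "standard deviation will rather be 1.8 mmol/l than 2.4 mmol/l (estimated reduction of 30"%).
- **Sample size (Sample size calculation).** For sizing, "we considered the deviation of [A^−^] at the time point T5 (120 min) compared to baseline T1 (0 min) applying a" t test. The result: "We set the level of significance to 5% and the power to 80% resulting in 21 patients per group".
- **Test (Analysis procedure).** Normally distributed data are compared between groups with a two-sample t test. "Level of significance for all calculations is defined at 5"%, with no statement of one or two sides.

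The article does not say which SD was entered for which arm.

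**The concern.** The argument for 1.8 runs through the phosphate supplement, which the control arm does not receive. On that argument the control arm keeps the 2.4 observed with Jonosteril® alone, and only the treatment arm moves to 1.8. If the calculation used 1.8 for both arms, it credited the control arm with a benefit of a product it is not given, and the stated power is too high.

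At stake is how far the 80% can be relied on. The primary objective is to show superiority on [A⁻], and the sample size statement tells readers what chance the trial has of doing so at the expected effect. The percentage in the same sentence also fails a simple check, so it is unclear which inputs were used.

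**Working it through.** **Inputs**

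- Difference: 0.60 × 2.67 = 1.602 mmol/l (Power considerations).
- SDs: 2.4 and 1.8 mmol/l (Power considerations).
- n = 21 per group, 1:1, level 5%, target power 80% (Sample size calculation).
- Sidedness: not stated. Two-sided is assumed because it reproduces 21 exactly; one-sided results are shown as well.

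**Formula**

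Standard error of the difference: SE = √[(SD_control² + SD_treatment²)/n]. Noncentrality: 1.602/SE. Power is the probability that a noncentral t variable with 2n − 2 = 40 degrees of freedom exceeds the critical value (2.021 two-sided, 1.684 one-sided; in the two-sided case the opposite tail is negligible).

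**Step 1: reproduce the plan's figure.** SD 1.8 in both arms: SE = √(6.48/21) = 0.555; noncentrality = 1.602/0.555 = 2.88; two-sided power = 80.3%. With 20 per group, power is 78.3%, so 21 is the smallest n that reaches 80%. This matches the stated sample size.

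**Step 2: use the SDs that the text argues for.** SD 2.4 control, 1.8 treatment: SE = √[(5.76 + 3.24)/21] = √(9.00/21) = 0.655; noncentrality = 1.602/0.655 = 2.45; two-sided power = 66.6%. The Welch form gives 66.4%. A simulation of 200,000 trials gives 66.6% (pooled) and 66.3% (Welch).

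**Step 3: vary the assumptions** (difference 1.602, t test)

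| SD control / treatment | Two-sided: power at 21 | Two-sided: n per group for 80% | One-sided: power at 21 | One-sided: n per group for 80% |
|---|---|---|---|---|
| 1.8 / 1.8 | 80.3% | 21 | 88.3% | 17 |
| 2.4 / 1.8 | 66.6% | 29 | 77.7% | 23 |
| 2.4 / 2.4 | 56.0% | 37 | 68.5% | 29 |
| 2.4 / 1.68 | 68.6% | 28 | 79.3% | 22 |
| 1.68 / 1.68 | 85.4% | 19 | 91.8% | 15 |

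Only the two-sided calculation with 1.8 in both arms gives 21.

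**Step 4: detectable difference.** With 21 per group, SD 2.4/1.8 and a two-sided test, 80% power is reached at 1.88 mmol/l. That is 1.88/2.67 = 70% of the expected fall, whereas the article's own expectation goes up to 60%.

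**Step 5: the percentage.** 1 − 1.8/2.4 = 0.25, a 25% reduction. A 30% reduction would give 2.4 × 0.70 = 1.68. As the table shows, 1.68 does not yield 21 under a t test either.

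**The case against.** Four points can be made on the plan's side.

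1. **Sidedness is open.** The article gives only 5%, and the objective is directional. One-sided at 5% with SD 2.4/1.8, power is 77.7%, close to the target. With 2.4/1.68 (taking the 30% literally), the one-sided normal approximation gives (1.645 + 0.842)² × (5.76 + 2.82)/1.602² = 20.7, which rounds up to 21. So one cannot say flatly that no other route leads to 21. But that route needs a one-sided test, an SD that contradicts the printed 1.8, and an approximation where the article names a t test; the t test itself needs 22. This limits the certainty of the 66% figure and does not restore 80%.

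2. **The sentence with 1.8 names no arm.** It could be a single planning SD for the trial. That is possible, but the sentence is drawn as a consequence of the range being one that "will be lower in the treatment compared to the control group", and no reason is given for a lower SD among controls. The 2.4/1.8 pair is therefore an inference from the reasoning, not a stated input. The control volumes may also differ somewhat from the 4000 ml of the earlier study, although the article itself applies those data to the control regimen.

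3. **A reader might infer that an equal-variance test is planned, in conflict with the predicted unequal SDs.** The article does not support this. It names a two-sample t test without saying which form, and at 21 per group the choice hardly matters (66.6% against 66.4%).

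4. **A reader might infer that a null result will be taken as proof of no effect.** Nothing in the article says so. It describes a phase II trial with an explorative purpose. That softens the consequence, but the article still states a formal level, power and sample size, and these should agree with its own inputs.

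**Conclusion.** The concern holds in this form: under a two-sided 5% t test, 80% power with 21 per group requires SD 1.8 in both arms, and the article gives grounds for 1.8 in the treatment arm only. With 2.4 in the control arm and 1.8 in the treatment arm, power for 1.602 mmol/l is 66% to 67%. The chance of missing that effect is then about one in three instead of one in five. If the test is one-sided at 5%, power is about 78%, also below the stated figure. The reduction from 2.4 to 1.8 is 25%, which is a plain slip that does not drive the sample size.

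This rests on three assumptions: a two-sided test, a control-arm SD that stays at the earlier 2.4, and a reading of 1.8 as the treatment-arm SD. The point concerns the stated power. It does not affect the type I error, the endpoint or the conduct of the trial.

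**What to change.** Keep 42 randomised patients and amend the sections Power considerations and Sample size calculation as follows:

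- State whether the test is one-sided or two-sided.
- State the SD assumed for each arm. If 1.8 is meant for the control arm too, give the reason.
- With 2.4 (control) and 1.8 (treatment), restate the two-sided power as about 66% for 1.602 mmol/l, or equivalently a detectable difference of about 1.88 mmol/l at 80% power.
- Correct 30% to 25%.

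Naming the Welch form of the t test is optional; it does not materially change the power.

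The cost is rewording two paragraphs and accepting a less favourable power statement. Restoring 80% power under these SDs would instead take 29 per group, or 58 randomised (16 more). That is not asked for here, given the explorative purpose.
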